#### Data collection and analysis.

The principal investigator [name] together with CB, both experienced in qualitative research, will conduct the semi-structured interviews at each university campus to collect subjective opinions and explore different points of view of the interviewed participants, being this technique a way of obtaining valuable information for the study [37]. The interviews will be video and audio-recorded to be later systematically transcribed verbatim. Atlas.ti software will be used for coding and data management [38].

The systematic text condensation proposed by Malterud [39], based on Georgi’s psychological phenomenological method [40] will be used for the qualitative data analysis. This analysis was created to develop the information reported by the participants in the interviews taking into account the recognition and importance of the researcher’s point of view on the subject and consists of 4 steps: 1. A general impression. 2. The identification of meaning units related to the phenomenological focus studied. 3. Coding the meaning units and grouping them by themes, considering the interviews. 4. Synthesis of the themes and categories.

The interviews will explore perceptions of spinal pain, including its causes, intensity, frequency, impact on work, and management strategies. Additionally, participants will discuss posture and ergonomics, focusing on the relationship between prolonged sitting and spinal pain, workplace ergonomics, and adaptive postural changes. Another key theme will be exercise and active breaks, exploring views on exercise for pain prevention, previous experiences with active breaks, types of exercises preferred, and barriers to implementation. Finally, participants will reflect on the feasibility of a web-based intervention and the digital platform, including preferences for accessing exercise tutorials, the potential for integrating an online program into their work routine, and the perceived usefulness of digital health resources. These insights will directly inform the exercise program’s design in the quantitative phase, ensuring it aligns with participants’ needs and workplace constraints. The semi-structured interview guide is provided in S1 File.

### Connection phase

In the context of addressing musculoskeletal spinal pain among office workers engaged in sedentary work, the qualitative phase is crucial for understanding how to integrate active breaks into their daily routines effectively and ensure high adherence tailored to their specific needs.

Upon analysing the qualitative data, the researchers will develop the content and materials (such as videos and informational dossiers) for the active break intervention. These materials will be hosted on the university’s virtual campus, which participants regularly access for work-related activities. Ensuring that the materials align with the experiences and needs of office workers with spinal pain will enhance usability and engagement. The intervention’s content, delivery, and communication will be guided by themes from the qualitative analysis, especially participants’ motivational barriers, preferences, and perceived feasible exercises. For example, if time constraints are a key barrier, short, flexible sessions will be prioritised; if visual instruction is preferred, video content will be emphasised.

The intervention will be delivered via Sakai [41], an open-source Learning Management System chosen for its familiarity and ease of use. This platform was chosen to ensure familiarity and ease of use for participants, as it is already utilised in their daily work routines. The intervention will be implemented asynchronously through the Sakai platform, allowing participants to complete the exercises at flexible times during work hours. The intervention will include media content (depending on participants’ needs) featuring low-dosage exercises focused on stretching and postural strengthening. These exercises will primarily target the different spine regions and adjacent areas such as the shoulders and hips. The primary goal is to interrupt sedentary time and promote movement variability of the spine [42].

A specialised physiotherapist with expertise in occupational health will oversee the program, providing remote supervision to guide participants and address any concerns. While the intervention is self-directed, participants will have direct access to the physiotherapist via email and platform messaging for any inquiries related to exercise execution, discomfort, or adherence difficulties. Additionally, if participants experience persistent difficulties or require further support, video consultations can be arranged upon request.

The asynchronous format was chosen to maximise flexibility and accessibility, allowing participants to engage with the intervention at convenient times without requiring real-time coordination. This is particularly relevant in office settings with varying workloads, where synchronous formats could limit participation [43]. Asynchronous telehealth interventions, particularly those with well-designed, interactive platforms that provide tailored information and self-management strategies, enhance adherence and engagement by empowering participants to manage their conditions effectively. This approach maximises accessibility and minimises barriers such as irrelevant content, information overload, and the impersonal nature of telehealth. Addressing these challenges, including support for individuals with low digital literacy, is crucial to fostering consistent engagement and self-efficacy [44].

Based on the qualitative findings, strategies such as periodic reminders, motivational messages, or personalised follow-up may be used to support engagement. These approaches are supported by existing literature, which highlights their effectiveness in improving adherence in digital health interventions [45].

### Quantitative phase

#### Design.

A two-arm cluster randomised controlled trial will be conducted following the recommendations of the CONSORT checklist [46]. A six-week online intervention will be carried out using exercise videos, taking into account the current scientific evidence and the results of the previous phase. The intervention will align with established guidelines [47], which emphasises therapeutic exercise, including strengthening exercises, mobility and stretching routines, and general physical activity, to improve musculoskeletal function and address musculoskeletal disorders.

In this study aimed at reducing musculoskeletal spinal pain among university office workers, two distinct interventions are being employed: the Intervention Group and the Control Group.

The Intervention Group will implement a six-week therapeutic exercise intervention in their workplace environment, following the program content developed in the previous phase.

Conversely, participants in the Control Group will be placed on a waiting list, advised to maintain their regular daily activities, and working hours. Upon completion of the questionnaires after the six weeks, they will gain access to the platform, receiving identical content to that of the Intervention Group.

#### Recruitment and sampling method.

The recruitment process will commence after the completion of the connection phase, once the qualitative data have been analysed and integrated into the design and development of the web-based intervention platform. This ensures that participants’ perspectives and workplace realities inform the intervention before implementation.

Participants in the quantitative phase will be recruited separately from the qualitative phase, following the sequential exploratory mixed-methods design [30]. However, office workers who participated in the qualitative phase will be encouraged to join the intervention trial, allowing for continuity while maintaining the opportunity to recruit a broader sample.

The inclusion and exclusion criteria for the quantitative phase will remain identical to those of the qualitative phase to ensure consistency in participant characteristics. Recruitment will involve emailing all office workers across the University of Lleida campuses. The lead author will oversee participant selection, conducting interviews to verify eligibility based on the established criteria. During these interviews, participants will be provided with a detailed explanation of the intervention, including its purpose, procedures, and expected level of participation.

To ensure ethical compliance, all participants will be required to sign an informed consent form before enrolment in the study. The informed consent document is provided in S2 File.

#### Sample size calculation.

The GRANMO calculator has been used to obtain the sample size. The study by Kenneth et al [48], has been taken for reference with a minimum significant difference in pain intensity of 1.5 and a standard deviation of 1.5, considering an alpha risk of 0.05 and a statistical power of 95% to reject the null hypothesis, the minimum number of participants per group necessary will be 33 accounting for an expected 20% dropout rate.

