#### Randomisation: type and sequence generation.

Participants in the study will be assigned to either the Intervention Group or the Control Group through cluster randomisation. The six campuses of the University will be randomised into either group to prevent contamination between groups. A 1:1 ratio will be maintained to ensure an equal distribution of campuses between the experimental and control clusters. The randomisation will be conducted using Study Randomizer, a web-based service, to ensure unbiased allocation [49].

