#### Statistical analysis.

Descriptive statistics will be used to summarise the demographic and baseline characteristics of participants. Categorical variables (e.g., gender, educational level) will be compared between control and intervention group using Chi-square tests or Fisher’s exact tests, as appropriate, while continuous variables (e.g., age) will be compared using independent-samples t-tests for normally distributed variables or Mann–Whitney U tests if the data are not normally distributed. The Shapiro-Wilk test and Q-Q plots will be employed to assess normality. If the data meet normality assumptions (p > 0.05), parametric tests will be applied; otherwise, non-parametric tests will be used.

Within-group comparisons (before- vs. after-intervention) will be conducted using paired t-tests for normally distributed variables, and the Wilcoxon signed-rank test will be applied for variables not meeting normality assumptions. Changes from baseline between the intervention and control groups (before and after differences) will be evaluated using independent-samples t-tests for normally distributed data, or Mann–Whitney U tests for non-normal data. Clinically significant changes will be assessed using criteria established in previously reviewed studies.

Mixed-effects models will be employed to evaluate the effect of the intervention over time, taking into account repeated measures. A linear mixed-effects model will be applied to outcomes that are approximately normally distributed, with random intercepts included to account for within-subject variability. If an outcome clearly violates normality assumptions even after exploration or transformation, a generalized linear mixed model (GLMM) with an appropriate link function (e.g., logit for binary outcomes) may be considered. These models will adjust for potential confounders such as age, gender, educational level, spinal pathologies, job tasks, and adherence. Statistical significance will be set at a p-value of less than 0.05. Mixed-effects models are appropriate for this cluster-randomised design with repeated measures, as they account for both fixed effects and within-subject variability. Sample size was estimated assuming a moderate effect size, an ICC of 0.05, alpha = 0.05, and 80% power.

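### The protocol gives two incompatible bases for one sample size, and its 33 per group carries no design effect, so the stated 95% power does not hold for six randomised campuses

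*Protocol article*

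**What the plan says.** The Sample size calculation section uses "a minimum significant difference in pain intensity of 1.5 and a standard deviation of 1.5". It sets alpha at 0.05 and power at 95%, and concludes that "the minimum number of participants per group necessary will be 33 accounting for an expected 20% dropout rate". It mentions no intracluster correlation, cluster size or design effect.

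The section on randomisation sets the unit of allocation: "The six campuses of the University will be randomised into either group to prevent contamination between groups". The campuses are split 1:1 between the arms, which makes three per arm.

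The last sentence of the Statistical analysis section returns to the sample size: "Sample size was estimated assuming a moderate effect size, an ICC of 0.05, alpha = 0.05, and 80% power". It gives no number for the moderate effect and no resulting sample size.

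**The concern.** Both statements describe, as already done, the sizing of the same trial. One has an effect of 1.5/1.5 = 1.0 SD, 95% power and no clustering. The other has a 'moderate' effect, 80% power and an ICC of 0.05. They cannot both be the source of 33 per group.

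A design effect is also missing from the only sample size given. The protocol names an ICC but does not apply it to that figure, although whole campuses are randomised.

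At stake is the power claim for pain intensity, the outcome on which the trial is sized. A reader cannot tell whether the trial claims 95% power for a full-SD effect or 80% for a moderate one, and might take a null result as stronger evidence against a moderate effect than the design can give.

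**Working it through.** **Inputs.** Difference 1.5, SD 1.5, alpha 0.05, power 95%, dropout 20% and 33 per group come from the Sample size calculation section. ICC 0.05, a 'moderate' effect and 80% power come from the Statistical analysis section. Six campuses at 1:1, so k = 3 per arm, come from the randomisation section. Assumptions made here: a two-sided test (sidedness is not stated, but two-sided reproduces 33), equal campus sizes, and 'moderate' between 0.5 and 0.8 SD because no number is given.

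**1. Reproduce 33.** n = 2 × (1.960 + 1.645)² × (1.5/1.5)² = 25.99, so 26 per group. Dropout: 26/0.8 = 32.5, so 33. The match is exact with a design effect of 1. One-sided at 95% power, or two-sided at 90%, would give 22, raised to 28; two-sided at 80% would give 16, raised to 20.

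**2. Power for 1.5 points with clustering.** With m analysed per campus, design effect DE = 1 + (m − 1) × 0.05, and SE = 1.5 × √(2 × DE/(3m)). Power is computed by the normal approximation and by the noncentral t distribution with 6 − 2 = 4 degrees of freedom.

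| Analysed per arm | m | DE | SE | 1.5/SE | Power, normal | Power, t with 4 df |
|---|---|---|---|---|---|---|
| 26 (after dropout) | 8.67 | 1.383 | 0.489 | 3.07 | 87% | 64% |
| 33 (no dropout) | 11 | 1.50 | 0.452 | 3.32 | 91% | 70% |

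At an ICC of 0.01 with 26 per arm, the figures are 93.5% and 73.9%. At an ICC of 0.10 they are 77.4% and 53.9%.

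**3. Can the second basis give 33?** At 0.5 SD and 80% power, the individually randomised formula already needs 63 per arm. With 33 analysed per arm, DE = 1.50 and the standardised SE is √(2 × 1.50/33) = 0.3015:

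| 'Moderate' read as | Effect/SE | Power, normal | Power, t with 4 df |
|---|---|---|---|
| 0.5 SD | 1.66 | 38% | 25% |
| 0.8 SD | 2.65 | 76% | 52% |

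Neither end of the range reaches 80%, even with no dropout.

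**4. Ceiling set by three campuses per arm.** As m grows without limit, the standardised SE tends to √(2 × 0.05/3) = 0.183. The power ceilings are:

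| Effect | Ceiling, normal | Ceiling, t with 4 df |
|---|---|---|
| 0.50 SD | 78.2% | 54.6% |
| 0.51 SD | 79.8% | 56.2% |
| 0.52 SD | 81.3% | 57.7% |
| 0.60 SD | 90.8% | 69.4% |
| 0.70 SD | 97.0% | 81.4% |

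The normal ceiling passes 80% just above 0.51 SD, and the 4-df ceiling near 0.7 SD.

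**The case against.** Four points on the other side deserve weight.

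- **The arithmetic of 33 is right for individual randomisation.** This stands. The fault is that the formula does not match the design, and that a second basis conflicts with it.
- **The 4-df figures describe a test that the protocol does not name.** This also stands. The Statistical analysis section plans participant-level tests and mixed-effects models, with no campus-level test or small-sample correction. A reader might infer that true power is simply 64%; that holds only if such a correction is used. On the normal approximation the shortfall is from 95% to 87%, or to 91% with no dropout. It is smaller, but still a shortfall.
- **'Moderate' has no number.** A reader might infer that 80% power is out of reach with six campuses whatever the enrolment. The documents do not support that without a condition: it is true at 0.5 SD, but by the normal approximation it reverses at 0.52 SD. Baseline adjustment that reduced both variance components (correlation 0.3) would lift the normal ceiling at 0.5 SD to 81.9%, though the 4-df ceiling only to 58.4%.
- **An ICC of 0.05 with 80% power is met for the 1.5-point difference** (87%, normal, at 26 completers). True on that approximation, but the sentence pairs these inputs with a moderate effect, and there it fails.

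Low power also does not make the trial uninformative about moderate effects, since a confidence interval would still be reported. None of these points reconciles the two sections or puts a design effect into 33.

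**Conclusion.** Wrong as written. The two stated bases are incompatible, and this needs no assumption beyond reading them together. The 33 per group is the individually randomised figure, so the promised "a statistical power of 95% to reject the null hypothesis" is not delivered once the protocol's own ICC is applied to three campuses per arm. The sizes in step 2 rest on that ICC and on equal campuses; unequal campuses would lower power further at the same enrolment.

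That the second basis cannot produce 33 holds across the whole 0.5 to 0.8 SD range. The ceiling below 80% is a narrower statement: it holds at 0.5 SD by both methods, and should be reported with that condition attached.

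**What to change.** Reconcile the two sections into one calculation in the Sample size calculation section. It should state the difference, the SD, the ICC of 0.05 (moved there from the Statistical analysis section, its only source), three campuses per arm, the expected completers per campus, the test or degrees-of-freedom basis, and the resulting power. On the current inputs and equal campuses, that is about 9 completers per campus and 87% power by the normal approximation, or 64% with 4 degrees of freedom.

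Remove the conflicting moderate-effect and 80% power statement, and say that the trial is not powered for a 0.5 SD effect. If the authors in fact sized the trial on the second basis, they should say so, give the effect size as a number, and show the sample size that follows.

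The cost is protocol wording and a less favourable power figure. No extra enrolment is required. For scale, restoring 95% for 1.5 points by recruitment alone would take 45 analysed per arm (45/0.8 = 56.25, so 57 enrolled) by the normal approximation, or 243 analysed (243/0.8 = 303.75, so 304 enrolled) with 4 degrees of freedom.

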#### Randomisation: type and sequence generation.

Participants in the study will be assigned to either the Intervention Group or the Control Group through cluster randomisation. The six campuses of the University will be randomised into either group to prevent contamination between groups. A 1:1 ratio will be maintained to ensure an equal distribution of campuses between the experimental and control clusters. The randomisation will be conducted using Study Randomizer, a web-based service, to ensure unbiased allocation [49].

#### Allocation concealment mechanism and implementation.

To ensure that allocation is concealed, one of the researchers will randomly create the codes in opaque envelopes with the username and password for participants to log into the web platform.

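### Individual login envelopes cannot conceal an allocation made by campus, and the visible text does not place campus randomisation after recruitment and baseline

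*Protocol article*

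**What the plan says.** All references are to the protocol article.

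- **Unit of allocation** (Randomisation: type and sequence generation): "The six campuses of the University will be randomised into either group to prevent contamination between groups". The ratio is also set at campus level: "A 1:1 ratio will be maintained to ensure an equal distribution of campuses between the experimental and control clusters". On how the allocation is generated: "The randomisation will be conducted using Study Randomizer, a web-based service, to ensure unbiased allocation". No time point is given.
- **Concealment** (Allocation concealment mechanism and implementation): "one of the researchers will randomly create the codes in opaque envelopes with the username and password". The stated purpose is to conceal allocation. The section does not say when the envelopes are prepared or handed out, or whether their preparer is separate from the recruiter.
- **Recruitment** (Recruitment and sampling method): the only timing statement is "The recruitment process will commence after the completion of the connection phase". Workers are approached individually: "Recruitment will involve emailing all office workers across the University of Lleida campuses". Selection is by interview: "The lead author will oversee participant selection, conducting interviews to verify eligibility based on the established criteria". At that interview, before consent, "participants will be provided with a detailed explanation of the intervention, including its purpose, procedures, and expected level of participation".
- **Blinding**: participants are not blinded. The evaluators' blinding rests on coded data. Nothing is said about whether the lead author knows the campus allocation.
- **Outcome** (Primary outcome; Data collection and analysis): pain intensity on a 0 to 10 VAS, self-reported online at baseline and at six weeks.

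**The concern.** A sealed envelope conceals allocation when it hides the next individual's assignment from the person deciding whether to enrol that individual. In this trial no individual assignment exists to be hidden, because everyone on a campus shares one arm. The section therefore claims a protection that its device cannot give.

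The usual protection in a cluster trial with individual recruitment is the order of steps: identify, consent and measure participants first, then allocate clusters. The visible text does not state that order. If campus arms were known during recruitment, three things could follow:

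- The interviewer could, even unintentionally, apply the criteria that need judgement differently by arm.
- Workers could volunteer differently depending on whether their campus starts now or goes on the six-week waiting list.
- Participants could score their baseline VAS knowing their arm.

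Each of these would weaken the comparability that randomisation should provide, for an unblinded, self-reported primary outcome. The Limitations section accepts that volunteers tend to be more motivated, but does not consider that this might differ between arms.

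**Working it through.** The plan gives no figure for concealment, so the check is mainly a comparison of sections plus a count.

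**1. How many assignments there are to conceal.** Six campuses split 3 and 3 give C(6,3) = 20 possible allocations. The unit is the campus.

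**2. How many envelopes there would be.** The Sample size calculation section gives 33 per group, so 2 × 33 = 66 participants. That figure reproduces for individual randomisation: with difference 1.5, SD 1.5, two-sided alpha 0.05 and power 95%, n = 2 × (1.960 + 1.645)² × 1.5²/1.5² = 25.99, so 26 per group, and 26/0.80 = 32.5, so 33. It is used here only to count envelopes. The average is 66/6 = 11 participants per campus. Knowing one participant's arm gives away the arm of everyone else on that campus, about 10 others on average.

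**3. What the envelopes do under each possible order of steps.**

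- *Campuses randomised before or during recruitment.* The arm follows from the workplace. The sealed login hides nothing from a recruiter or volunteer who knows the campus's arm.
- *Campuses randomised one at a time as each finishes baseline.* The remaining campuses become predictable. Once three campuses in one arm are known, the rest must be in the other. Once five are known, the sixth is fixed. Envelopes do not change this.
- *All campuses randomised in one step after baseline is complete everywhere.* Allocation is concealed, but by the timing. The envelopes only deliver credentials.

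In none of the three do the envelopes conceal the allocation.

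**4. Whether another stated safeguard fills the gap.**

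- The web service generates the sequence; the text does not say who holds the result or when it is released.
- The start of recruitment is tied to the end of the connection phase, not to randomisation.
- The blinding section covers evaluators' data coding, not the recruiter.
- Fig 1 is not shown. Its caption lists enrolment before allocation, so it may imply an order.

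**5. What the analysis could recover.** The Statistical analysis section compares changes from baseline and adjusts mixed models for factors such as age, gender, educational level, spinal pathologies and job tasks. These can offset part of a measured imbalance. They would not remove differences between arms in unmeasured factors, such as expectation of benefit.

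**The case against.** The strongest reply is that the timing part argues from silence. No sentence says that campuses are randomised before recruitment, and the schedule figure is not available to this review. A reader might infer that the allocation is known while workers are being recruited. The document does not support that, so the timing point stands only as an order that needs to be stated. Even if Fig 1 shows enrolment before allocation, that would not by itself require all six campuses to finish baseline first, and it would not make the envelopes a campus-level device.

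Several design features also limit the risk. The same email goes to all office workers, and one set of criteria applies everywhere. Many criteria are thresholds assessed on a recruitment form (pain for more than three months, at least 80% of working hours seated, activity and step limits), which narrows the interviewer's discretion. Controls receive identical content after six weeks, which weakens the incentive to volunteer by arm. These points are fair. They reduce the exposure without removing it: ability to exercise safely still needs judgement, and a six-week wait may still affect who comes forward.

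Two further inferences go too far. One is to set an assumed baseline VAS gap between arms against the 1.5-point target difference and treat the ratio as the bias. The planned comparison is of changes from baseline, so a baseline gap does not carry over one for one, and the document gives no basis for the part that would. The other is that no analysis could help: the change scores and adjusted models can offset measured imbalance in part.

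**Conclusion.** The mismatch between device and unit is in the text and holds whatever the order of steps: individual login envelopes do not conceal an allocation made across six campuses. This goes beyond missing detail, because the article names a mechanism and claims a property for it that it does not have.

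Differential recruitment and arm-aware baseline reporting are a risk, not a demonstrated bias. The risk depends on campus arms being known to the recruiter or to workers before recruitment and baseline are complete, which the visible text neither states nor rules out. Its size cannot be estimated from the document. The adjusted analyses would offset it only partly. The correction is worth making because the primary outcome is self-reported and unblinded, the lead author selects participants by interview, and the change is cheap.

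**What to change.** Replace the envelope claim with a cluster-level mechanism:

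- Randomise all six campuses in one step, only after eligibility interviews, consent and baseline questionnaires are complete on every campus.
- Have the sequence generated and held by someone not involved in recruitment, and tell the lead author the result only after that point.
- Describe the envelopes, if kept, as a way of delivering login details.
- State the order of steps in the text and check that Fig 1 agrees with it.

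If allocation cannot wait, keep the recruiter unaware of campus allocation and give identical information on all campuses until baseline is complete.

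The change affects only the order of steps and who holds the sequence. The small downside is that early recruits wait until the last campus has finished baseline.
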